### **Monitoring / Audit**

The trial investigators will permit trial-related monitoring, audits and/or regulatory inspections, providing direct access to source data and documents as required by the WNHS Ethics committee.

### **Quality control and quality assurance**

The trial will be conducted in compliance with Good Clinical Practice, as outlined in The Australian Clinical Trial Handbook (2006). Quality assurance has been addressed through consultation with neonatologists and lactation consultants at the study setting. Review of the trial protocol is to be completed by the Scientific Advisory Committee, Governance and Ethics Committees at KEMH.

### **Ethics**

The research nurse ([name], neonatal nurse) or principal research associate ([name], neonatally trained nurse and lactation consultant) will approach mothers of preterm infants that meet the trial criteria. The mothers will be provided with a verbal explanation of the study and will be requested to read the provided written study information sheet. The nurse or associate will offer to return later to find out whether the mother would like to participate with her infant. Any requested additional information will be provided verbally and written consent obtained. (see Appendices B, C for Study Information and Consent forms). The lactation consultants employed by NCCU have been involved in the study design and will support the research nurse, research associate and patients when appropriate.

It is possible that the use of a teat that facilitates the sucking dynamics of a breastfeed may maintain physiological stability as well as provide 'training' that may advance the development of breastfeeding skills, shorten the transition to full breastfeeding, and increase breastfeeding duration. The knowledge gained from the study has the potential to form the basis for evidence-based modification of feeding policies for preterm infants. When initiating breastfeeding for very preterm infants, current advice often includes use a nipple shield to aid attachment, and breast expression prior to offering a breastfeed. There is no/little evidence for this advice. Evaluation of maturation of SSB coordination may also provide markers such as strength of vacuum that are predictive of breastfeeding success. In this case simple monitoring may provide a means for determining readiness for the transition to full breastfeeding.

The coordinating principal investigator (CPI) of the study is also a consultant neonatologist and the Director of the Neonatology Clinical Care Unit (study site). On occasion the CPI may be the assigned neonatologist responsible for the medical care of study participants. The CPI will not be directly involved in recruitment of participants or in data collection. All potential participants will be verbally encouraged to decline or consent freely and voluntarily with assurances that their decision will not impact in any way on their infant's present or future care.

#### **Budget, financing, indemnity and insurance**

The CPI is employed and insured by KEMH, while A/[name] and [name] are employed and insured by The University of Western Australia. [name]'s salary is partly funded by a Telethon research grant (\$40,539) that is administered by Women's and Infants' Research foundation, and the Centre for Neonatal Research and Education has provided a donation of \$53,000.

Teats for the intervention group will be donated by the manufacturer, Medela AG. Each infant (n=60) will require 30 starter and 60 advanced Calmita and 5 Calma teats.

Employment of a research nurse will be funded by the Centre for Neonatal Research and Education, The University of Western Australia.

|                          |              |
|--------------------------|--------------|
| Annual Rate ANF 1.8      | \$76,846.00  |
| Weeks per annum          | 52.14        |
| Weekly Salary            | \$1,473.84   |
| Hours per week           | 40           |
| Hourly Rate              | \$36.85      |
| On-Costs          |              |
| Workers Comp 3.19%       | \$2,451.39   |
| Superannuation 9.25%     | \$7,108.26   |
| Long Service Leave 2.50% | \$1,921.15   |
| Annual Leave 7.69%       | \$5,909.46   |
| Sick Leave 3.85%         | \$2,958.57   |
| Processing costs 3.77%   | \$2,897.09   |
| Full Year 1 FTE 30.25%   | \$100,091.92 |
| Full Year at 0.5 FTE     | \$ 50,045.96 |
| With GST                 | \$ 55,050.56 |

The following research support will be given in kind

[name] Level A Step 08 1.0 FTE = \$85,942 – Telethon funding = \$45,403

A/[name] Level B Step 02 @ 1 day / week = \$22,700

W/[name] Level E Step 01 @ 1 day / month = \$7,980

[name] @ 1 day / fortnight = \$10,720

### **Publication**

The trial will be registered with the publicly accessible Australian New Zealand Clinical Trials Registry following confirmation of Ethics approval and prior to commencement of the trial. Within 6 months of the completion of data analysis, study findings will be disseminated through oral presentations, written reports, and manuscripts will be submitted to peer-reviewed professional journals for publication.

Study participants that request to be informed of study results will be provided with a plain language report and/or copies of published papers as requested.

## Appendix A: Preterm Infant Breastfeeding Behavior Scale (PIBBS)\*

| Scale items                                                                 | Maturational steps                                                          | Score |
|-----------------------------------------------------------------------------|-----------------------------------------------------------------------------|-------|
| Rooting                                                                     | Did not root                                                                | 0     |
|                                                                             | Showed some rooting behavior                                                | 1     |
|                                                                             | Showed obvious rooting behavior                                             | 2     |
| Areolar grasp
(how much of the
breast was inside
the baby's mouth) | None, the mouth only touched the nipple                                     | 0     |
|                                                                             | Part of the nipple                                                          | 1     |
|                                                                             | The whole nipple, not the areola                                            | 2     |
|                                                                             | The nipple and some of the areola                                           | 3     |
| Latched on and
fixed to the breast                                       | Did not latch on at all so the mother felt it                               | 0     |
|                                                                             | Latched on for $\leq 5$ min                                                 | 1     |
|                                                                             | Latched on for 6-10 min                                                     | 2     |
|                                                                             | Latched on for $\geq 11$ -15 min                                            | 3     |
| Sucking                                                                     | No sucking or licking                                                       | 0     |
|                                                                             | Licking and tasting, but no sucking                                         | 1     |
|                                                                             | Single sucks, occasional short sucking
bursts (2-9 sucks)                | 2     |
|                                                                             | Repeated short sucking bursts, occasional
long bursts ( $\geq 10$ sucks) | 3     |
|                                                                             | Repeated ( $\geq 2$ ) long sucking bursts                                   |       |
| Longest sucking burst                                                       | 1 – 5 consecutive sucks                                                     | 1     |
|                                                                             | 6 – 10 consecutive sucks                                                    | 2     |
|                                                                             | 11 – 15 consecutive sucks                                                   | 3     |
|                                                                             | 16 – 20 consecutive sucks                                                   | 4     |
|                                                                             | 21 – 25 consecutive sucks                                                   | 5     |
|                                                                             | $\geq 26$ -30 consecutive sucks                                             | 6     |
| Swallowing                                                                  | Swallowing was not noticed                                                  | 0     |
|                                                                             | Occasional swallowing was seen                                              | 1     |
|                                                                             | Repeated swallowing was noticed                                             | 2     |

\*Nyqvist et al, 1996

## Appendix D: Case Report Form, Master

(complete at recruitment)

**Mother's name:**

Mobile no:

e-mail: (if unable to contact via phone)

Mother's birth date:

☐ Mother has requested study report

**Baby's name:** Male / Female

Date of birth: Birth gestation: Birth weight: SGA/AGA/LGA

Ventilation days: CPAP days: IVH grade: Sepsis:

### SCN Study schedule (B=breast, NS= nipple shield, record dates, teat type)

| CGA          | bottle | B + NS                                  | B - NS | Full B | Empty B |
|--------------|--------|-----------------------------------------|--------|--------|---------|
| birth gest = |        |                                         |        |        |         |
| 33/40        |        |                                         |        |        |         |
| 34/40        |        |                                         |        |        |         |
| 35/40        |        |                                         |        |        |         |
| 36/40        |        |                                         |        |        |         |
| 37/40        |        |                                         |        |        |         |
| 38/40        |        |                                         |        |        |         |
|              |        |                                         |        |        |         |
| CGA          | date   |                                         |        |        |         |
|              |        | first sucked a full feed                |        |        |         |
|              |        | first suck all feeds over a 24hr period |        |        |         |

Date and CGA at transfer / discharge:

Calma teats given? ☐ Yes ☐ NA

### Breastfeeding background data (complete at recruitment)

"Please tell us about your breastfeeding experience and plans"

Have you breastfed any previous babies?

1. no
2. yes – I breastfed for \_\_\_\_\_ days / months (range if > 1 baby breastfed)

For how long do you plan to breastfeed this baby? \_\_\_\_\_ months

How important is BF to you?

1. Not at all important
2. Not important
3. Important
4. Very important

Thinking back over the last 24 hours, what is the total amount of milk you have expressed? \_\_\_\_\_ mL (baby is \_\_\_\_\_ days old)

addressograph sticker

addressograph sticker

## Appendix E: Case Report Form Monitored feed

Date:

CGA: 33      34      35      36      Other:

Postnatal days:                      Naked weight: \_\_\_\_\_g

Prescribed feed volume: \_\_\_\_\_mL    ☐ 3hrly ☐ 2hrly    \_\_\_\_\_IGT : \_\_\_\_\_suck

### Breastfeed

Breast fullness            ☐ Full (last expressed  $\geq$  3hr)    ☐ Empty (last expressed  $\leq$  1hr)

Nipple shield            ☐ No                                      ☐ Yes    size:

### Bottle feed

☐ Calmita starter    ☐ Calmita advanced                      ☐ Conventional

Pre feed weight:                      Pre feed milk sample                      ☐

Post feed weight:                      Post feed milk sample                      ☐

Total volume transferred:

Heart rate range:

SaO2 range:

☐ Resp plethysmography

☐ Intraoral vacuum

☐ PIBBS completed by mother

PIBBS score: \_\_\_\_\_

☐ 24hr production and milk samples collected    Result \_\_\_\_\_mL

Total number of feeds in last 7 days: \_\_\_\_\_

Total number of oral feeds: \_\_\_\_\_

Of these, total breastfeeds: \_\_\_\_\_

**Adverse events** – details eg. bradycardia, apnoea, interventions required

**Notes:**

## Appendix F: Case Report Form Follow up interview

addressograph sticker

Corrected age (weeks): 2 6 12

Please tell me is (baby) still breastfeeding or receiving your breastmilk?

NO → Can you tell me when (baby) last received a breastmilk feed?  
(record date and corrected age)

What were your reasons for weaning? \_\_\_\_\_

Thank for participation in study → no further follow up required

YES → I would like to ask some questions about how your baby is feeding.

Thinking back over the last 24 hours, how many times has your baby fed? \_\_\_\_\_

How many of these were breastfeeds? \_\_\_\_\_

Do you use a nipple shield when breastfeeding? Yes No

(if not fully breastfeeding...)

How many of the feeds were bottle-feeds? \_\_\_\_\_

Of those, how many were breastmilk feeds?

How many full feeds were given by bottle?

How many top up feeds were given by bottle?

What type of teat/s do you use to bottle feed?

Are you having any difficulties with feeding?

If any questions or concerns are raised with regard to feeding, refer mother to

SCN home visiting nurse (if home visiting is still being provided)

KEMH Breastfeeding Centre

GP as appropriate

ABA as appropriate

Thank you for taking the time to answer these questions today. I will call again when your baby is \_\_\_\_ weeks corrected age.

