### Trial Aims

1. To track maturation of intraoral vacuum and SSB coordination as well as physiological stability of breastfeeding preterm infants over time and determine if this is related to increased effectiveness and efficiency of breastfeeding. We hypothesize that improvement in breastfeeding efficiency (mL/min) and effectiveness (total mL transferred) will be associated with changes in one or more of vacuum strength (average and changes across a feed), consistency of sucking (number of sucks/suck bursts per feed) and SSB coordination.
2. To explore the effect of the volume of milk in the breast on milk transfer during breastfeeding at 34 weeks CGA. Our hypothesis is that more milk in the breast will result in a higher volume of milk being transferred by the infant at the breastfeed.
3. (Optional) To explore the effect of nipple shield use on milk transfer at 35 weeks CGA. The hypothesis is that nipple shields improve attachment and breastmilk transfer
2. To compare SSB coordination and maturation during breastfeeding with bottle feeding with a Calmita teat, and bottle-feeding with a conventional teat. Our hypothesis is that infants fed with a Calmita teat will experience less apnoea and bradycardia and reach full oral feeds more rapidly than those fed with a standard teat.
3. To determine the effect of a vacuum triggered teat (Calmita during stay in study hospital, and Calma used for top up feeds post discharge/transfer from the study hospital) on the timing of achievement of full breastfeeding and on breastfeeding duration.

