### Trial Design

#### Trial endpoints

The primary endpoint for this trial is total breastfeed volume (mL) transferred at a breastfeed, measured at 33, 34, 35 weeks and term CGA

Secondary endpoints to be measured during monitored feeds are  
efficiency (mL/min)

- total suck duration

- total suck bursts
- mean, peak and baseline intraoral vacuum (mmHg)
- oxygen saturation range
- heart rate range
- incidence of bradycardia
- incidence of oxygen desaturation

The following feeding endpoints will also be determined

- timing of achievement of full oral feeds
- timing of achievement of full breastfeeding
- breastfeeding duration (monitored up to 3 months post-term)

1. A randomized controlled clinical trial will be undertaken with random allocation in blocks of size 4 to either a control group or an intervention group. Study design is depicted in Figure 1.
2. A pilot study of up to 5 infants will be completed prior to commencement of the trial to test and refine the set-up and duration of monitoring sessions.
3. Study participant data and milk samples will be re-identifiable, with an identification code assigned to each infant. A master sheet that matches infant identity to identification codes will be stored in a password-protected electronic file on a lap top computer. All paper copies of case report forms will be stored in a locked filing cabinet at The University of Western Australia.
4. The effect of a vacuum-controlled bottle-feeding teat (Calmita and Calma teats, Medela AG) on breastfeeding outcomes will be evaluated in this clinical trial. A shut-off valve is incorporated into the Calmita teat so milk flows only when the infant creates a vacuum. Venting prevents collapse of the teat. There are two versions of Calmita with different threshold levels for the vacuum-controlled valve of  $-10 \pm 5$  mmHg (starter teat) and  $-30 \pm 15$  mmHg (advanced teat). We have previously investigated a prototype of this product but wish to carry out more extensive studies on the final product.

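### Full breastfeeding and breastfeeding duration are undefined endpoints, and no form dates the first full breastfeeding or the last feed at the breast

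*Combined protocol and SAP*

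**What the plan says.** The Trial endpoints section lists three feeding endpoints: "timing of achievement of full oral feeds", "timing of achievement of full breastfeeding" and "breastfeeding duration (monitored up to 3 months post-term". The last of the Trial Aims is to determine the effect of the vacuum-triggered teat "on the timing of achievement of full breastfeeding and on breastfeeding duration". No section gives an operational definition of full breastfeeding, or says whether duration means feeding at the breast or receiving any breastmilk.

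The forms collect the following.

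- **Appendix D (master form)** has date and corrected gestational age (CGA) columns for two milestones: "first sucked a full feed" and "first suck all feeds over a 24hr period". Neither separates breast from bottle.
- **Appendix E (monitored feed)** has 7-day counts of all feeds, oral feeds and breastfeeds. It has no milestone date and no field for top-ups.
- **Appendix F (calls at 2, 6 and 12 weeks corrected age)** opens with "Please tell me is (baby) still breastfeeding or receiving your breastmilk". A NO leads to "Can you tell me when (baby) last received a breastmilk feed", then the reasons for weaning, and follow-up ends. A YES leads to counts for the past 24 hours: all feeds, breastfeeds and, for infants not fully breastfed, bottle feeds, breastmilk bottle feeds, full bottle feeds and top-ups.

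The statistical analysis section describes linear mixed models for the monitored feeds. It names no method for the timing or duration endpoints.

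**The concern.** The Background explains that the earlier trial could not supply the teat after discharge, and so could not show whether continued use affects duration or achievement of full breastfeeding. Calma teats are provided at discharge in this trial to cover that period. These two endpoints are therefore the main test of the post-discharge part of the intervention.

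Two things are at stake. First, an endpoint worded as a timing has no date on any form. Second, the randomised product is a bottle teat. It could plausibly prolong bottle-feeding of expressed milk without prolonging feeding at the breast, and a stop date that counts breastmilk by any route would record that as breastfeeding. Dates not asked for at the call may not be recoverable accurately later.

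**Working it through.** The plan states no figure on this point, so there is none to reproduce. The check matches endpoints to form fields and then computes the gaps between scheduled contacts.

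**1. Endpoints against fields**

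| Endpoint | Dated field | What can be derived |
|---|---|---|
| Full oral feeds | Appendix D, first all-suck 24 hours | Exact date, if reached before the infant leaves the study hospital |
| Full breastfeeding | None | Status at each call, from the 24-hour counts on the YES branch |
| Breastfeeding duration | Appendix F, last breastmilk feed | Exact for any breastmilk; bracketed only for feeding at the breast |

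**2. Gaps for time to full breastfeeding**

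Inputs: the last scheduled inpatient form at 35 weeks CGA, the term visit, and calls at 2, 6 and 12 weeks (Table 1, Appendix F). Assumption: term is 40 weeks CGA, so the 35-week form lies at 35 − 40 = −5 weeks. Gap = next contact − previous contact.

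- With a form completed at the term visit (−5, 0, 2, 6, 12): 0 − (−5) = 5; 2 − 0 = 2; 6 − 2 = 4; 12 − 6 = 6 weeks.
- Calls alone, with no inpatient form after 35 weeks (−5, 2, 6, 12): 2 − (−5) = 7; 6 − 2 = 4; 12 − 6 = 6 weeks.

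If the term visit falls earlier or later than 40 weeks, the first two gaps change but still add to 7. For infants who stay and have forms at 36, 37 or 38 weeks (rows in Appendix D), the gap from the last form to the 2-week call is 42 − 36 = 6, 42 − 37 = 5 or 42 − 38 = 4 weeks.

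These gaps are a best case at the inpatient and term end. On Appendix E a breastfeed followed by a top-up still counts as a breastfeed, so those counts give only approximate status.

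**3. Events missed altogether**

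If full breastfeeding starts and all breastmilk stops between two contacts, the next call goes down the NO branch. That branch does not ask about full breastfeeding, so the infant looks the same as one who never reached it. A spell of full breastfeeding that lapses to mixed feeding before the next call is lost in the same way.

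**4. Duration**

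The recorded stop is the last breastmilk feed, which is never earlier than the last feed at the breast. Hence recorded duration − at-breast duration = length of any later period on expressed milk alone, which is zero or more.

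As an illustration on the form's own call times, take an infant with some breastfeeds at the 2-week call, none at the 6-week call, and breastmilk still being given at 12 weeks. The at-breast stop lies between 2 and 6 weeks. Any-breastmilk duration is at least 12 weeks, so by the last call it exceeds at-breast duration by 12 − 6 = 6 to 12 − 2 = 10 weeks.

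**The case against.** The strongest reply is that the data are coarse, not absent. At each call the YES branch shows whether the infant is fully breastfed, so time to full breastfeeding can be analysed as interval-censored, or as prevalence at 2, 6 and 12 weeks. An infant who has left the breast but still receives breastmilk shows zero breastfeeds and is identifiable. Under an any-breastmilk definition, Appendix F captures duration exactly. In hospital, the test weighs at every breastfeed, the 7-day counts and the 24-hour record before discharge help to locate an early transition. These are also not primary endpoints.

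Most of this stands. A reader might infer that time to full breastfeeding cannot be derived at all and that recorded duration is simply wrong. The documents support neither reading: the first event can be bracketed between contacts, and the second date is wrong only under a definition that the protocol does not give. A reader might also infer that any error differs between arms. That is plausible for a bottle teat, but the documents give no figure for it.

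The reply does not remove the core. The plan names no interval-censored or prevalence analysis, the inpatient records do not cover the period after discharge, and the NO branch closes follow-up with both dates unasked.

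**Conclusion.** The point holds as a gap in definition and data capture for two non-primary endpoints. Time to full breastfeeding is interval-censored, with scheduled gaps of 2 to 6 weeks if a form is completed at the term visit and 4 to 7 weeks on calls alone with no inpatient form after 35 weeks. Some spells would be missed entirely. The recorded stop date measures any-breastmilk duration; if feeding at the breast is meant, it overstates duration by the length of any later period on expressed milk alone. How many infants this affects cannot be estimated from the documents.

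The gap sizes assume that term is 40 weeks CGA and that contacts occur on schedule. A smaller related gap is that Appendix F has no question to recover the all-suck date for an infant transferred before full oral feeds. The documents do not say how many such infants to expect.

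This is a cheap improvement worth making before the calls begin, not a defect that undermines the trial. The primary endpoint, volume transferred at a breastfeed, and the sample size do not depend on it.

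**What to change.** 1. In Trial endpoints, define full breastfeeding (including whether top-ups are allowed and over what period) and state whether breastfeeding duration means feeding at the breast or any breastmilk. The choice is the sponsor's.
2. Add the date of first full breastfeeding to Appendices D and F. In Appendix F, ask it on the NO branch too.
3. Add the date of the last feed at the breast to Appendix F, separate from the last breastmilk date. Ask it on the NO branch, and on the YES branch when the 24-hour breastfeed count is zero.
4. For infants transferred before full oral feeds, ask at the first call for the date of the first all-suck 24 hours.
5. In the statistical section, report at-breast and any-breastmilk duration separately, and analyse time to full breastfeeding as interval-censored where the date is missing.

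The cost is three date questions on existing forms, about a minute per call, and some recall error in the dates given. No extra contact or participant is needed.

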### *Effect of delivery of milk via different teats on SSB co-ordination in preterm infants*

For preterm infants who have demonstrated the ability to attach and suck at the breast, in the absence of the breastfeeding mother it is common for some intra-gastric tube feeds to be replaced with bottle feeds with the rationale that more frequent suck feeds accelerate the progression to full oral feeding. This translates to the situation where it is rare for an infant not to receive a bottle during their hospital stay. One of the problems associated with bottle-feeding using conventional teats is the occurrence of apnoea, which is more frequent than with breastfeeding. Most recently we have shown that when hospitalised preterm infants are fed with a teat that does not release milk unless the infant creates a vacuum (Calmita, Medela AG, Switzerland), a sucking action similar to breastfeeding is facilitated, and this is

associated with improved breastfeeding rates at discharge and decreased length of hospital stay when compared to infants fed with a conventional teat. The incidence of any breastfeeding at discharge was similar between the groups (*Simmer et al, Novel feeding system to promote establishment of breastfeeds after preterm birth: a randomised controlled trial. Submitted*). It is possible that use of the Calmita teat facilitates coordination of SSB by the infant's regulation of milk flow. If so one would expect a reduction in apnoea and bradycardia during feeding with Calmita compared to the conventional teat. Further after discharge many preterm infants continue to require top up feeds from a bottle while transitioning to full breastfeeding. As the Calmita teat was not available following discharge from hospital it was not possible to determine whether continued use a vacuum controlled teat such as the Calmita or Calma (Medela AG, Switzerland) for top up feeds post discharge influences duration of breastfeeding and achievement of full breastfeeding

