that remain in the Neonatal Nursery beyond 35 weeks CGA will be invited to continue with weekly monitored breastfeeds and bottle feeds until the time of transfer or discharge.

7. Each week the mother will be given the option of collecting a small milk sample (0.5-1.0mL) before and after every pumping or breastfeed over a 24-hour period to allow more accurate estimation of breast fullness. We expect milk production to increase over the study period therefore one 24-hour collection will not be sufficient.
8. Prior to discharge each mother will be asked to record expression volumes and the milk transfer at the breast (test weigh as in point 5) for a 24-hour period. This will be compared to the normal term infant ranges for 24 hour milk production/milk transfer.
9. At discharge/transfer the mother in the intervention group will receive Calma (term) teats to use for top up feeds while establishing breastfeeding.
10. The mother and infant will be invited to return to KEMH at term corrected age for monitoring of SSB during a breastfeed

The researchers will monitor compliance with use of the allocated teats and pre-post feed weighing during participants' hospital stay, and will be responsible for providing Calma teats to the intervention group mothers prior to the infants' transfer or discharge from KEMH.

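### No case report form asks directly about adverse events on home Calma feeds, and a mother who reports weaning is not asked about teat use or feeding problems since the previous call

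*Combined protocol and SAP*

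**What the plan says.** The last of the Trial Aims defines the vacuum-triggered teat intervention as Calmita in hospital plus "Calma used for top up feeds post discharge/transfer from the study hospital". Treatment of Participants, point 9, puts this into practice: "At discharge/transfer the mother in the intervention group will receive Calma (term) teats to use for top up feeds while establishing breastfeeding". The Background expects real use at home, since "after discharge many preterm infants continue to require top up feeds from a bottle while transitioning to full breastfeeding".

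The researchers undertake to "monitor compliance with use of the allocated teats and pre-post feed weighing during participants' hospital stay". No matching undertaking is given for the period at home.

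After discharge the plan has an invited visit at term corrected age, at which a breastfeed is monitored, and telephone calls at 2, 6 and 12 weeks corrected age using Appendix F. That form splits at its first question, on whether the infant is still breastfeeding or receiving the mother's milk.

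- **YES branch.** After the prompt "if not fully breastfeeding" come questions on bottle feeds, including "What type of teat/s do you use to bottle feed". The branch also asks "Are you having any difficulties with feeding", and the form carries a referral list for any concerns.
- **NO branch.** The mother is asked when the infant last had breastmilk and why she weaned. The form then says "Thank for participation in study → no further follow up required".

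**The concern.** A teat supplied by the trial and used at home is part of what is being tested, so one would expect the forms to ask whether it was used and whether feeds with it caused trouble. The section on criteria for terminating the trial makes the trial-level stop depend on adverse events reported from monitoring or from the trial teat. For Calma, no form supplies that information by a direct question.

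The branching in Appendix F adds a second gap. The teat and difficulty questions are never put to a mother who has weaned, so the time just before weaning is not covered for the infants in whom breastfeeding ended. Once follow-up has closed, the information cannot be recovered. What is at stake is safety and exposure data, not the efficacy comparison.

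**Working it through.** The plan states no figure on this point, so there is nothing to reproduce. The check is to compare the forms and then work out the interval lengths.

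**Step 1: what each form asks about Calma.**

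| Form | When used | Teat information | Adverse events or problems |
|---|---|---|---|
| Appendix D (master) | Hospital stay, to discharge or transfer | Whether Calma was supplied | None for Calma |
| Appendix E (monitored feed) | Monitored feeds | Boxes for Calmita starter, Calmita advanced and conventional; none for Calma | Open adverse-event line for the feed |
| Appendix F, YES branch | 2, 6 and 12 weeks | Current teat type, if not fully breastfeeding | Open question on current difficulties |
| Appendix F, NO branch | The call at which weaning is reported | None | Reasons for weaning only |

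Items asking directly for adverse events on home Calma feeds: 0. Items on teat type after discharge: 1, in the YES branch only and in the present tense.

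**Step 2: the term visit.** Table 1 and Treatment of Participants, point 10, provide one monitored breastfeed at term and no monitored bottle feed after discharge. Appendix E could be used at this visit, because its age field has an open option and it has an adverse-event line and a notes field. It does not ask which teat is used at home. The visit is therefore a contact at which a problem could be volunteered, but not one at which Calma use or Calma problems are solicited.

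**Step 3: interval lengths.** The call ages come from Table 1 and Appendix F. The documents give no discharge age. As an assumption, take discharge at 35 to 38 weeks corrected gestational age and term as 40 weeks. The lower end matches the last planned in-hospital monitored feed, and the upper end matches the last row of the Appendix D grid.

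- Discharge to term visit: 40 − 38 = 2 weeks to 40 − 35 = 5 weeks.
- Term visit to first call: 2 weeks.
- Discharge to first call: (40 + 2) − 38 = 4 weeks to (40 + 2) − 35 = 7 weeks.
- First to second call: 6 − 2 = 4 weeks.
- Second to third call: 12 − 6 = 6 weeks.

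**Step 4: what is lost per infant.** For each weaned infant, at most one record of teat type and feeding difficulty is missing: the one covering the last call (or discharge) up to weaning. That span is at most 4 weeks if weaning falls between the first two calls, and at most 6 weeks if it falls between the last two. If weaning comes before the first call, the span runs from discharge to weaning, at most about 4 to 7 weeks, and no teat record after discharge exists. The documents give no weaning rate, so the number of infants affected is not estimated.

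**The case against.** The best counter-argument is that nothing the plan sets out to analyse needs these data. The aim involving Calma concerns the timing of full breastfeeding and breastfeeding duration. The bradycardia and desaturation endpoints are defined for monitored feeds, the analysis is by intention to treat, and no exposure-based analysis is planned. This stands, and it is why the point is a cheap improvement and not a defect in the efficacy comparison.

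Two further arguments stand in part. First, the termination criteria act on events that have been reported and describe safety monitoring as continuous, so spontaneous reports can reach that review. The information and consent appendices are not available, so any reporting route described to parents there cannot be checked. Second, the question on reasons for weaning could bring out a feeding problem, and an infant weaned late may already have answers from one or two earlier calls. Neither supplies a direct question about home Calma feeds, or covers teat use between the last call and weaning.

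A reader might infer more than the documents support:

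- **That infants go 4 to 7 weeks after discharge without contact.** The term visit falls inside that period for those who attend. The figure is time without a teat or difficulty question.
- **That Appendix F collects nothing before weaning.** Mothers still breastfeeding or giving breastmilk are asked about difficulties at each call, and those also bottle-feeding are asked the teat type.
- **That the plan breaks its own promise to record adverse effects at every feed.** The Assessment of Safety section may mean feeds observed in hospital, so no breach is shown.
- **That breastfeeding duration is biased.** The NO branch captures the date of the last breastmilk feed.

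**Conclusion.** The point holds in a limited form. Calma at home is part of the evaluated intervention, yet no case report form directly asks about adverse events on Calma feeds. When weaning is reported, teat use and feeding problems since the previous call are not solicited. The loss is at most one record per weaned infant, covering up to 4 or 6 weeks between calls, or up to about 4 to 7 weeks before the first call. The last range rests on assumed discharge at 38 to 35 weeks and term at 40 weeks; the other two follow from the call schedule. An infant weaned before the 2-week call has no teat record after discharge, whether or not the term visit is attended.

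The safety review can still act on spontaneous reports, and no efficacy endpoint is affected. Time after weaning is not counted as lost, because Calma is meant for top-ups while breastfeeding is being established. The point is worth acting on because the change is small and the missing answers cannot be recovered later.

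**What to change.** In Appendix F, move the teat-type and feeding-difficulty questions ahead of the YES/NO split and word them to cover the time since discharge or last contact. Add one fixed question, identical in both arms, on any feed-related choking, colour change, pause in breathing or unplanned medical review over the same period. Ask these items at every call, including the one at which weaning is reported, and at the term visit when it is attended. No calls after weaning are needed. If the forms are left as they are, limit teat-safety conclusions to Calmita use in hospital.

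The cost is two questions moved and reworded, one added, the same short set used at an existing visit, and no extra calls or procedures. There are three downsides:

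- Parent recall is less precise than monitoring. It would span 4 and 6 weeks between the later calls. Under the assumed discharge ages, the first call would span 2 weeks for those who attended the term visit and 4 to 7 weeks for those who did not.
- Mothers know which teat they use, so reports may differ by arm for reasons unrelated to the teat.
- With about 30 infants per arm, counts will be small.

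The answers should therefore be used descriptively for safety review and not for a formal comparison between arms.
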